### Randomization

Patients fulfilling criteria for selection for this study will be randomized to receive an intervention or to be in the control group. Randomization will be done by concealed, centrally allocated, computer-generated random numbers.

### Procedure

All consecutive HIV-positive patients visiting two out-patient clinics will be asked to provide informed consent to receive a baseline assessment (using the data collection instruments) and screening for alcohol problems. If eligible – meaning an AUDIT questionnaire score of 8 to 19 for men or 7 to 19 for women – a second informed consent will be asked before randomization into the intervention or control group. Patients with a score of 20 and above on the AUDIT (with probable alcohol dependence) will be referred for further management (according to local standard procedures). The research assistant nurse will randomize patients by checking the random numbers that allocate the case to the intervention arm or control arms. The intervention or control procedures will be carried out in all patients, after which they will be followed up at 3 and 12 months (which are standard visit intervals for the follow-up of the HIV care). The research assistant performing the follow-up assessments will be blinded to the intervention allocation of the participant. In the event of a drop-out, at least six individual attempts will be made to contact patients by telephone and letter. Even if a contact was not successful at either follow-up point, further attempts will be made at any next follow-up point. Sampling will occur throughout all hours of clinic operation over a 3-month period. Patients will be offered a drink (soda, juice) during the interviews.

### Data collection instruments

Eight instruments (questionnaires) will be used to collect data. All questionnaires will be administered in English or Tswana, the two languages predominantly spoken by nearly all clinic patients. The questionnaires will be administered at baseline and every follow up visit.

#### Sociodemographic characteristics

A researcher-designed questionnaire will be used to record information on participants’ age, gender, population group, language, educational level, marital status, highest educational qualification, source of income and residential status.

#### Health-related quality of life

The WHOQoL-HIVBREF is based on the WHOQOL-HIV measure, one of the two World Health Organization (WHO) quality-of-life instruments for the use in HIV-infected populations
[32,33]. The WHOQoL-HIVBREF evaluates the quality of life in six domains and 31 questions.

#### Depression

Symptoms of depression will be assessed using the 10-item version of the Centers for Epidemiologic Studies Depression Scale
[34]. The Centers for Epidemiologic Studies Depression Scale has been widely used in studies on the relationship between HIV and depression
[35]. The sensitivity and specificity of the Centers for Epidemiologic Studies Depression Scale 20-item survey has been reported to average 80% and 70%, respectively, compared with formal diagnostic interview
[36]. We will also identify patients who experience more severe depressive symptoms by distinguishing those scoring ≥15 out of 30 on the Centers for Epidemiologic Studies Depression Scale 10-item survey
[34].

#### Sexual behavior

To study the sexual behavior of HIV patients, and specifically those who consume hazardous amounts of alcohol before and after intervention, we included questions on sexual behavior.

#### Internalized AIDS stigma

We will use the seven-item internalized AIDS-related stigma scale for people infected with HIV. Items reflect self-defacing beliefs and negative perceptions of people living with HIV/AIDS. In previous studies including South Africa, with the same scale, a Cronbach alpha reliability coefficient of 0.72 to 0.76 was found
[37].

#### Alcohol consumption

The 10-item AUDIT assesses alcohol consumption level (three items), symptoms of alcohol dependence (three items), and problems associated with alcohol use (four items)
[38]. Responses to items on the AUDIT are rated on a four-point Likert scale from 0 to 4, with a maximum score of 40 points. AUDIT scores higher than 19 indicate more severe levels of risk; scores of 8 to 19 in men and 7 to 19 in women indicate a tendency to problematic drinking. The AUDIT shows excellent sensitivity and specificity in detecting Mini-International Neuropsychiatric Interview-defined dependence/abuse (area under the receiver-operating characteristic curve = 0.96) in HIV patients in South Africa
[5].

To reduce the stigma of alcohol use, the WHO suggests integrating the screening of alcohol use with screening for other health-related behaviors
[38]. For this reason, two questions will be asked on the use of tobacco products and anthropometric measurements will be taken to assess the risk factor of overweight (height, weight and waist circumference).

#### HIV-related information

A researcher-designed patient information extraction sheet will be used to record information related to the HIV infection and will include questions about date of first positive HIV test, start date for ART, ART regimen, co-infections and co-medication. The patient file will be used to obtain additional information. The computerized laboratory data system will be used to obtain the laboratory results. At follow-up, CD4 cell counts and viral load will be obtained from the computerized laboratory data system.

#### Assessment of adherence to antiretroviral therapy

For assessing adherence to ART we will use three tools.

##### Self-reported adherence by recall of missed doses during last 7 days

This tool is easy to use and is significantly associated with virological and immunological outcomes
[39].

##### Visual Analog Scale

The 30-day Visual Analog Scale provides an overall adherence assessment for a 1-month period. The Visual Analog Scale has been validated in resource-limited settings
[40,41]. Adherence levels assessed from the Visual Analog Scale are defined as follows: full adherence, 100%; partial adherence, between ≥95% and <100%; and non-adherence, <95% of prescribed doses taken in the past 30 days. The Visual Analog Scale will be assessed at baseline for patients who are already on ART and at any follow-up visit if the patient is on ART.

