### Objectives

The objectives of the screening phase are: to measure the prevalence of alcohol consumption among out-patients with HIV; and to describe drinking patterns, health status, quality of life, sexual behavior and adherence levels among out-patients with HIV, and identify hazardous drinkers needing intervention.

The objectives of the intervention phase are: to compare the level of alcohol consumption, health status, quality of life, level of adherence to ART and sexual behavior among hazardous drinkers between pre-intervention and 3 and 12 months after the intervention; and to compare levels of and changes in alcohol consumption, adherence level to ART, quality of life, health status and number of patients with virological and immunological failure, between intervention and control groups at 3 and 12 months.

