### Inclusion criteria

Patients who are 18 years and older, with HIV-1 infection and who are visiting selected outpatient clinics for their HIV care will be eligible for this study. Patients with hazardous alcohol use will be selected using the AUDIT questionnaire (hazardous drinkers score 8 to 19 for men and 7 to 19 for women).

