### Exclusion criteria

Patients with mental impairment, patients already undergoing alcohol reduction treatment and pregnant women will be excluded from this study.

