### Data analysis

Virological failure will be defined according to the definition in the South African national guidelines on HIV: a repeat HIV viral load ≥1,000 copies/ml after intense adherence assessment
[43]. Immunological failure will be defined according to the WHO definition: a fall of CD4 cell count to pre-therapy baseline (or below), or a 50% fall from the on-treatment peak value (if known), or a persistent CD4 cell count level below 100 cells/mm^3^[44].

Means, standard deviations, and percentages will be used for descriptive statistics. To examine differences between groups, the *t* test for continuous data and the chi-square test for categorical data will be used. Generalized linear model repeated measures 2×3 analysis of variance will be used for comparing observations (alcohol use score) across the three contact periods to demonstrate a treatment intervention×time interaction. To avoid possible bias from excluding patients with missing values, patterns of missing values will be analyzed. Multiple imputation methods using generalized estimating equating methods, based on all data available in the model, using five imputed datasets, will be used to impute missing data at all contact points (baseline and follow-up at 3 and 12 months). SPSS for Windows version 18.0 (SPSS, Inc., Chicago, IL, USA) will be used for calculations.

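### Follow-up adherence is compared in a set defined by ART status after randomization, and the treatment-failure comparison does not exclude untreated patients

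*Protocol article*

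**What the plan says.** All of this is in the Protocol article.

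- **Entry.** Under Inclusion criteria, adults with HIV-1 "visiting selected outpatient clinics for their HIV care will be eligible for this study", subject to the AUDIT range. ART is not mentioned. The Exclusion criteria read "Patients with mental impairment, patients already undergoing alcohol reduction treatment and pregnant women will be excluded from this study"; being off ART is not among them.
- **Adherence.** The Visual Analog Scale (VAS) is taken "at baseline for patients who are already on ART and at any follow-up visit if the patient is on ART". The 7-day recall and the pill count carry no separate rule, but both presuppose prescribed pills.
- **Comparisons.** The Objectives compare adherence levels and their changes between arms, and also the "number of patients with virological and immunological failure, between intervention and control groups at 3 and 12 months".
- **Failure definitions (Data analysis).** Virological failure is "a repeat HIV viral load ≥1,000 copies/ml after intense adherence assessment". Immunological failure has three alternative criteria: "a fall of CD4 cell count to pre-therapy baseline (or below"), a halving from the peak reached on treatment, or a CD4 count that stays under 100.
- **Methods (Data analysis).** Group differences are tested with t or chi-square tests. The one model named, a repeated-measures analysis of variance, is for the alcohol score. Missing data are multiply imputed at baseline, 3 and 12 months.
- **HIV-related information.** The ART start date is extracted.

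**The concern.** The VAS rule itself shows that some patients are expected to be off ART at entry and to start later. Whether a patient is on ART at 3 or 12 months is settled after allocation. The article's own reasoning allows the intervention to affect it: the Background links alcohol use to late presentation for HIV care (odds ratio 3.55) and to poor adherence, and the Hypothesis expects less drinking to improve adherence and health status.

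If the arms differ in who starts or stops ART, a comparison of everyone on ART at the visit mixes a change in adherence with a change in who is being measured. Randomization does not protect against that. The failure comparison has a related gap: the article does not say which patients can be counted. At stake are the adherence and treatment-failure results that would accompany the alcohol result in any case for policy use.

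**Working it through.** The only computed figure in the article is the AUDIT sample size. It does not bear on this point, so there is no stated figure to reproduce.

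**Step 1. Who contributes adherence data.** Applying the VAS rule to the four possible ART histories:

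| Baseline → visit | Baseline value | Visit value | In comparison of levels | Change defined |
|---|---|---|---|---|
| on → on | yes | yes | yes | yes |
| off → on (starter) | no | yes | yes | no |
| on → off (stopper) | yes | no | no | no |
| off → off | no | no | no | no |

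The levels comparison uses rows 1 and 2, and the change comparison uses row 1 only. The two are made in different patients. Neither set is all randomized patients or a subgroup fixed at baseline.

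**Step 2. How large the bias could be (assumed inputs).** Let *b* be the share on ART at baseline, *i* the share of the rest who start by the visit, and *s* the non-adherence risk in starters. Non-adherence in baseline-ART patients is set at 20% in both arms, so there is no true effect; stopping is ignored. Non-adherence among patients on ART at the visit is

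p = [0.20·b + s·(1 − b)·i] / [b + (1 − b)·i].

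Example with b = 0.75 and s = 0.35:
- Control, i = 0.30: (0.150 + 0.02625) / 0.825 = 0.2136.
- Intervention, i = 0.70: (0.150 + 0.06125) / 0.925 = 0.2284.
- Spurious difference: 1.5 percentage points.

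Range over i = 0.30 in control versus 0.50 or 0.70 in intervention, and s = 0.10 or 0.35:

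| On ART at baseline | Absolute spurious difference (points) |
|---|---|
| 90% | 0.2 to 0.6 |
| 75% | 0.5 to 1.5 |
| 50% | 1.0 to 2.7 |

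The sign depends on *s*: it favours the intervention when starters adhere better than established patients and goes against it when they adhere worse. With i = 0.30 in both arms the difference is zero.

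**Step 3. Who can be counted as a failure.** The first two immunological criteria refer to a pre-therapy value or an on-treatment peak, so a patient never on ART cannot meet them. The third, CD4 staying under 100, states no treatment condition and could be met without ART. The viral-load definition implies treatment, because it follows an adherence assessment, but states neither ART nor time on ART. As worded, untreated patients could add to the per-arm number.

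**Step 4. Does the denominator matter for power (assumed inputs)?** Take 96 per arm followed up (120 × 0.8), failure of 20% versus 10% among ART patients, a share *q* on ART, and off-ART patients counted as non-failures. The difference over all patients is q × 10 points; the risk ratio stays 0.10/0.20 = 0.50.

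| q | Difference, all patients | Power, all patients | Power, ART patients only |
|---|---|---|---|
| 100% | 10.0 | 49% | 49% |
| 90% | 9.0 | 45% | 45% |
| 75% | 7.5 | 38% | 39% |
| 50% | 5.0 | 26% | 28% |

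Restricting to ART patients loses no power against an all-patient denominator in these cases.

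**The case against.** The strongest reply is that the VAS sentence is a data-collection rule, not an analysis population. Recording adherence whenever a patient is on ART is ordinary, and the start date allows a baseline-ART subset to be formed later. Analysis sets for secondary outcomes are often left to the analysis plan. That is fair as far as it goes. But the article does state the comparison (levels and changes, between arms, at both visits) and the tests. Taken with the collection rule, those tests fall on whoever is on ART at the visit.

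It can also be said that one 20-minute alcohol session with no ART-initiation step is unlikely to move ART uptake much. This stands as a limit on size: without a difference between arms in starting or stopping, there is no bias. It is equally fair that adherence off ART is not applicable rather than missing, and that nothing says outright that it will be imputed. The imputation sentence makes no exception either, so this is a clarification only.

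Three stronger readings are tempting and are not supported:
- A reader might infer that adherence comparisons include patients off ART. The VAS rule excludes them.
- A reader might infer that failure counts are diluted. The Objectives give no denominator; off-ART patients would dilute a proportion, not a count; and through the CD4-below-100 criterion they could add cases instead.
- A reader might infer that a recent starter whose CD4 count has not yet risen is classed as failing. The definition requires a fall to the pre-therapy value, which such a patient does not plainly meet.

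**Conclusion.** The point holds in limited form. As written, the adherence comparison rests on a set defined after randomization, its level and change versions use different patients, and the failure comparison leaves open whether untreated patients count.

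Bias requires ART starting or stopping to differ by arm. Its size cannot be computed, because the article gives no ART share, start rate or stop rate. The 0.2 to 2.7 points shown rest entirely on assumed values and cover starting only. The case for change is that the better-defined comparison is available from data already collected, not that a large error has been shown. The AUDIT comparison on which the trial is sized is untouched.

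**What to change.** State that the between-arm comparisons of adherence, virological failure and immunological failure are made in patients on ART at randomization, identified from the extracted start date, with that number per arm as the denominator. This subset is fixed before allocation, so randomization still protects it.

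- Adjust the adherence comparison for its baseline value in place of the unadjusted test.
- Keep patients who later stop ART in the set. Because the VAS is not taken once ART has stopped, fix in advance how those visits are scored, and report their number by arm.
- Report patients who start ART after baseline separately, by arm, as description.
- State that adherence is not imputed for visits before ART was started.

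The cost is analysis wording: the start date and baseline VAS are already collected, and the article reports that recruitment is still under way. The downside is a smaller denominator for these secondary outcomes, which should be stated with the results.

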##### Pill count

A pill count compares the number of pills that were dispensed and that are remaining at the pill count. A percentage of adherence to ART will be calculated.

### Interventions

#### Control group

Patients in the control group will only receive a health education leaflet on responsible drinking. They will receive the brief intervention only after 12-month follow-up, if the intervention has proven to be successful.

#### Intervention group

Patients in the intervention group will first receive personalized feedback on the AUDIT results. A health education leaflet on responsible drinking will then be given and discussed. Subsequently, simple advice and brief counseling on reducing excessive drinking will be offered during a one-session, 20-minute intervention. Since there is a serious lack of resources in South Africa in HIV care, an efficient intervention has to be short and simple to incorporate into daily practice. Intervention methods whereby patients have to come back for more sessions might in daily practice be unsuccessful because of the time-consuming aspect for those who perform the intervention and because of an expected high patient drop-out rate. A short, one-session intervention has therefore been chosen to be tested in this trial. The brief intervention is based on the WHO brief intervention package for hazardous and harmful drinking
[42], which is based on the Information–Motivation–Behavioural Skills Model. The steps of brief counseling are: identify any alcohol-related problems mentioned in the interview; introduce the sensible drinking leaflet, and emphasize the idea of sensible limits, and make sure that patients realize that they are in the medium-risk drinking category; work through the first three sections of the problem-solving manual while mentioning the value of reviewing the other sections; describe drinking diary cards; identify a helper; and mention the 3-month and 12-month follow-up.

### Counselor training and intervention quality assurance

The intervention research assistants will be trained to deliver the interventions to the patients. The training consists of role play, general skills training techniques and training on HIV and sexual-related issues. A comprehensive manual for the brief intervention is available and will be used to guide the counseling session. The sites will be visited twice a week by one of the investigators to observe whether there is adherence to the protocol and to offer support and supervision to the research assistants. During regular research meetings, occurring problems will be discussed and solved.

### Data analysis

Virological failure will be defined according to the definition in the South African national guidelines on HIV: a repeat HIV viral load ≥1,000 copies/ml after intense adherence assessment
[43]. Immunological failure will be defined according to the WHO definition: a fall of CD4 cell count to pre-therapy baseline (or below), or a 50% fall from the on-treatment peak value (if known), or a persistent CD4 cell count level below 100 cells/mm^3^[44].

Means, standard deviations, and percentages will be used for descriptive statistics. To examine differences between groups, the *t* test for continuous data and the chi-square test for categorical data will be used. Generalized linear model repeated measures 2×3 analysis of variance will be used for comparing observations (alcohol use score) across the three contact periods to demonstrate a treatment intervention×time interaction. To avoid possible bias from excluding patients with missing values, patterns of missing values will be analyzed. Multiple imputation methods using generalized estimating equating methods, based on all data available in the model, using five imputed datasets, will be used to impute missing data at all contact points (baseline and follow-up at 3 and 12 months). SPSS for Windows version 18.0 (SPSS, Inc., Chicago, IL, USA) will be used for calculations.

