### Sample size calculation

The sample size was calculated using Open Epi
[29]. Based on the current AUDIT score of 12 among HIV patients, it is assumed that the intervention will reduce the current AUDIT score by 12% to 10.6
[30,31]. Based on this assumption, the estimated sample size will allow us with 80% power (5% level of significance) to detect the difference of 12% between the two groups. This will give a minimum of 99 patients per arm. It is expected that 20% of participants may be lost prior to completing the 3-month and 12-month follow-up assessments so that the final sample would be 120 per arm. A total of 240 HIV patients (with AUDIT scores 8 to 19 for men or 7 to 19 for women) will be recruited for the study.

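### For quality of life, the only between-arm method named is an unadjusted t test, and both levels and changes are asked for with neither named as the main result, although the baseline score is collected

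*Protocol article*

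**What the plan says.** All references are to the Protocol article, Methods/Design.

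- **Objectives.** The between-arm aim of the intervention phase, at 3 and 12 months, is "to compare levels of and changes in alcohol consumption, adherence level to ART, quality of life, health status", followed by counts of patients with treatment failure. Level and change stand side by side, and neither is named as the main result.
- **Data collection instruments.** "The questionnaires will be administered at baseline and every follow up visit". The WHOQoL-HIVBREF, with six domains, is one of these questionnaires, so each randomized patient should have a pre-intervention score on every domain.
- **Data analysis.** The general rule is "To examine differences between groups, the *t* test for continuous data and the chi-square test for categorical data will be used". The one longitudinal method carries its outcome in brackets: "Generalized linear model repeated measures 2×3 analysis of variance will be used for comparing observations (alcohol use score) across the three contact periods".

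No baseline covariate is named for any outcome.

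**The concern.** Read together, these sections give each WHOQoL-HIVBREF domain score two candidate between-arm results per visit: a t test on the follow-up level and a t test on the change from baseline. The first ignores the baseline score. The second subtracts all of it, which adds noise when the correlation between baseline and follow-up is below 0.5. A linear model that includes baseline as a covariate lets the data set the weight and is at least as precise as either, apart from one degree of freedom.

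Two things are at stake. Precision is given up on an outcome named in both the Objectives and the Hypothesis. And because the main result is not fixed, the same data could show a quality-of-life benefit by level and none by change, or the reverse. With six domains and two visits there are 6 × 2 = 12 between-arm questions, and 12 × 2 = 24 tests if each is answered in both forms.

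**Working it through.** **Inputs from the article (Sample size calculation).** 99 per arm before loss, 120 after allowing for loss, 20% expected loss, 80% power, 5% significance (taken as two-sided), and an AUDIT difference of 12 − 10.6 = 1.4.

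**The plan's own figure.** No SD is given, so 99 per arm can be reproduced only with an assumed one. With SD 3.5:

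n = 2 × (1.960 + 0.842)² × 3.5² / 1.4² ≈ 98.1, rounded up to 99.

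The standardized difference is then d = 1.4 / 3.5 = 0.40. This is an AUDIT figure. It is borrowed for quality of life purely as an illustration.

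**Patients analysed.** 120 × 0.8 = 96 per arm.

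**Variance of the arm difference.** Assume equal SDs at both times and correlation rho between baseline and follow-up. Relative to the level comparison:

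- level: 1
- change: 2(1 − rho)
- baseline-adjusted: 1 − rho²

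**Power.** The noncentrality of the level test is 0.40 × √(96/2) = 2.77. For the other two analyses, divide by the square root of the relative variance.

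| rho | Relative variance: level / change / adjusted | Noncentrality: level / change / adjusted | Power: level / change / adjusted | Gain over the better t test |
|---|---|---|---|---|
| 0.3 | 1 / 1.40 / 0.91 | 2.77 / 2.34 / 2.90 | 78.8% / 64.5% / 82.4% | 82.4 − 78.8 = 3.6 points |
| 0.5 | 1 / 1.00 / 0.75 | 2.77 / 2.77 / 3.20 | 78.8% / 78.8% / 89.0% | 89.0 − 78.8 = 10.2 points |
| 0.7 | 1 / 0.60 / 0.51 | 2.77 / 3.58 / 3.88 | 78.8% / 94.5% / 97.1% | 97.1 − 94.5 = 2.6 points |

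Which t test is the better one depends on rho: level below 0.5, change above it. The loss from relying on the worse one is larger: 82.4 − 64.5 = 17.9 points at rho = 0.3 (change) and 97.1 − 78.8 = 18.3 points at rho = 0.7 (level).

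**Agreement of the two t tests.** The level and change estimates have correlation (1 − rho)/√(2(1 − rho)), which is 0.59, 0.50 and 0.39 at rho = 0.3, 0.5 and 0.7. With d = 0.40 and 96 per arm, exactly one of the two tests is significant in about 27%, 23% and 21% of trials.

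**Why they part.** A chance baseline imbalance of b SD moves the level difference by rho × b and the change difference by (rho − 1) × b. For b = 0.2 and rho = 0.5, these are +0.10 and −0.10 SD. An imbalance of at least 0.2 SD has z = 0.2/√(2/96) = 1.39, a two-sided probability of about 17% per score.

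**The case against.** **The plan attacked is assembled, not stated.** No sentence says that quality of life will be t-tested on both level and change. The t test sentence follows one on descriptive statistics, speaks of groups rather than arms, and could also serve the screening phase. The phrase about levels and changes could be read as covering alcohol consumption alone. This stands as far as it goes: the double use of the t test is inferred. But no other between-group method is named for continuous data outside the alcohol score, and even on the narrow reading the unadjusted t test and its loss of precision remain.

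**An article leaves such detail to the full protocol or analysis plan.** That would answer a complaint of silence. Here the article names a method and asks for two forms of the comparison, so the point concerns what is stated.

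**The size is borrowed.** This is correct. Neither d nor rho comes from the documents for this outcome. The 10-point gain is the most favourable of the three correlations shown; at the other two it is about 3 to 4 points. The 96 per arm also sets aside the planned multiple imputation.

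**Stronger readings that do not hold.** A reader might infer that the t tests are biased. They are not: randomization keeps both unbiased in expectation, and each holds its own 5% level. A reader might also infer that the false-positive rate nearly doubles. With no true effect, at least one of the two tests is significant in about 8.8% to 9.4% of trials per score and visit, but that becomes the error rate only if either result would be accepted as proof, and the article does not say so. Finally, a reader might extend the point to health status, depression or CD4 count. Health status has no named instrument, and neither the depression score nor the CD4 count is in the list of between-arm comparisons.

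**Conclusion.** The point holds for the WHOQoL-HIVBREF domain scores at 3 and 12 months. The only between-arm method named for them makes no use of a baseline score that the trial collects, and the article does not say whether level or change is the main result. The cost is precision and the lack of one fixed answer; validity is not affected. Under d = 0.40, rho from 0.3 to 0.7, equal SDs and 96 per arm, all assumed for this outcome, adjustment gains about 3 to 10 power points over the better t test, and the two t tests disagree in about 21% to 27% of trials. The AUDIT score did not enter this check, since it has its own repeated-measures analysis, and quality of life did not set the sample size. The weight is therefore moderate: a worthwhile improvement at almost no cost.

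**What to change.** In Data analysis, state that each WHOQoL-HIVBREF domain score at 3 and at 12 months will be compared between arms by a linear model of the follow-up value on arm and the baseline value of the same score. The adjusted mean difference with its 95% CI is the single between-arm result for that score and visit. Change scores are reported as descriptive summaries only. In Objectives, align the wording so that level and change no longer stand as two unranked comparisons for quality of life.

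Apply the same model to any other continuous non-AUDIT outcome compared between arms only where a baseline value exists. That condition matters for adherence: the Visual Analog Scale is taken at baseline only in patients already on antiretroviral therapy.

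The cost is a sentence or two and one degree of freedom per model. No data, visits or patients are added. SPSS fits the model, and it can be run in each of the five planned imputed datasets. The article reports recruitment as ongoing, so the change can be made before any comparison by arm.

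### The 80% power is for one two-group AUDIT difference, but the only test tied to the alcohol score is a 2-df, non-directional arm-by-time interaction with baseline as a response

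*Protocol article*

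**What the plan says.** **Sample size calculation.** The starting point is a mean of 12 ("Based on the current AUDIT score of 12 among HIV patients"), and "it is assumed that the intervention will reduce the current AUDIT score by 12% to 10.6". The power statement is that "the estimated sample size will allow us with 80% power (5% level of significance) to detect the difference of 12% between the two groups". This gives 99 per arm, raised to 120 for an expected 20% loss. No SD, no correlation between visits and no time point are given.

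**Data analysis.** The alcohol score is named once, in the sentence on the 2×3 repeated-measures model: "analysis of variance will be used for comparing observations (alcohol use score) across the three contact periods to demonstrate a treatment" intervention×time interaction. The same section lists the contact points as baseline, 3 and 12 months. A separate, general sentence says that for group differences the *t* "test for continuous data and the chi-square test for categorical data will be used". It names neither AUDIT nor a visit.

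**Hypothesis and Objectives.** The hypothesis is directional: drinking falls more in the intervention arm. The objectives include comparing the arms on both level and change of alcohol consumption at 3 and 12 months.

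No analysis is labelled primary. The 2×3 model is read here as the main efficacy analysis because it alone names the alcohol score.

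**The concern.** The trial is sized for one comparison and analysed with another. A two-group mean difference has one degree of freedom and a direction. The interaction over three visits has two degrees of freedom and no direction, and it treats baseline as an outcome although allocation cannot affect it. It rejects for any departure from parallel profiles, whether the effect is sustained, fading or reversing.

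Baseline AUDIT is also limited by eligibility to 8–19 in men and 7–19 in women, while follow-up scores are not. Equal variances across the three levels are therefore doubtful, which is a further reason to use baseline as a covariate.

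Two later decisions depend on the result. Controls are to be offered the intervention after 12 months if it has succeeded, and the Outcomes section foresees possible use in national HIV care guidelines. The protocol does not say which visit or contrast defines success. Fading is plausible: the Background cites an HIV study whose 3-month gain was not sustained at 6 months, and this intervention is a single 20-minute session.

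**Working it through.** **Inputs from the protocol.** Means 12 and 10.6, so δ = 12 − 10.6 = 1.4. Power 80%, level 5% (sidedness not stated; two-sided assumed). 99 per arm before loss. 120 × 0.8 = 96 per arm expected to remain.

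**Inputs assumed.** SD σ, equal at all visits, and the correlations ρ between visits. Neither is in the protocol.

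**1. The plan's own figure.** For two means, n = 2σ²(z₀.₉₇₅ + z₀.₈₀)²/δ². Without an SD, 99 cannot be reproduced, but it can be solved for σ:

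σ = 1.4 × √(99/2) / (1.960 + 0.842) = 1.4 × 7.036 / 2.802 ≈ 3.52.

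(With δ = 1.44, exactly 12% of 12, σ ≈ 3.62; one-sided with δ = 1.4, σ ≈ 3.96.) The 99 is thus consistent with a 1-df comparison of two means at one time point.

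**2. The planned test.** Two arms by three visits gives (2 − 1)(3 − 1) = 2 df.

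**3. Power for a sustained effect (1.4 at both follow-ups), 99 per arm, σ = 3.516, equal ρ.**
- Interaction: noncentrality λ = nδ²/[3σ²(1 − ρ)]. At ρ = 0.5, λ = 99 × 1.96/(3 × 12.36 × 0.5) ≈ 10.5. On 2 and 392 df the power is 83%.
- Baseline-adjusted difference at one visit: noncentrality δ/[σ√(1 − ρ²)√(2/n)]. At ρ = 0.5 this is 1.4/(3.516 × 0.866 × 0.142) ≈ 3.23. On 195 df the power is 90%.

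| ρ | Interaction, 2 df | Baseline-adjusted, 1 df | n per arm for 80%: interaction / adjusted |
|---|---|---|---|
| 0.2 | 62% | 81% | 147 / 96 |
| 0.3 | 68% | 83% | 129 / 91 |
| 0.4 | 75% | 86% | 111 / 84 |
| 0.5 | 83% | 90% | 92 / 75 |
| 0.6 | 91% | 94% | 74 / 64 |

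**4. Timing.** Under the same assumptions, an effect of 1.4 at 3 months and none at 12 gives the same λ as a sustained effect. At ρ = 0.5 the interaction rejects 83% of the time in both cases, so its p-value cannot tell them apart.

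**5. Simulation with unequal correlations.** 96 per arm, SD 3.5. Correlations for baseline–3 months, baseline–12 months and 3–12 months ran from (0.4, 0.3, 0.5) to (0.6, 0.5, 0.6).
- Sustained effect: interaction about 72–87%; baseline-adjusted 12-month difference about 83–89%.
- Effect at 3 months only: interaction about 77–90%; baseline-adjusted 12-month difference about 5%.

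**6. A conditional figure.** If *t* tests on AUDIT at 3 and at 12 months were run as efficacy tests beside the interaction, each at 5%, at least one would reach p < 0.05 in about 12% of trials with no effect.

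**The case against.** **The interaction bears on the hypothesis.** A greater reduction is a differential change from baseline, which an arm-by-time interaction tests. This stands. The test is relevant; its weakness is that it carries neither direction nor time point.

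**Underpowering.** A reader might infer that the trial is underpowered. The documents do not support that. The interaction's power falls on both sides of 80% depending on a correlation the protocol does not give. An unadjusted *t* test at one visit, the comparison that was sized, has about 78% with 96 per arm, inside the interaction's range. Part of the gain from the alternative comes from baseline adjustment.

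**Multiplicity.** A reader might also infer that AUDIT gets three chances at 5% each. The *t*-test sentence is generic and could refer to baseline comparisons or other continuous outcomes. The 12% applies only if those tests are used for efficacy on AUDIT at both visits, which the text does not say.

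**A 3-month effect is real.** Detecting it is no error, and the planned means and SDs would show timing and direction. That is fair, but a descriptive reading of means is not a test or an interval for a named visit.

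**The article is condensed.** Follow-up contrasts may be specified in a fuller document. But the article does state the test and its purpose, and these do not match its own power statement. That mismatch is in the text.

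**Conclusion.** The point holds as a mismatch between what is powered and what is tested. The 80% was derived for one two-group difference and cannot be carried over to a 2-df interaction that includes baseline. A significant interaction alone would not establish lower drinking in the intervention arm at 3 or at 12 months.

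In the cases computed, the interaction is less powerful for a sustained effect than a 1-df baseline-adjusted comparison at one visit. The gap is 19 percentage points at ρ = 0.2 (62% against 81%) and 3 points at ρ = 0.6 (91% against 94%). All power figures rest on a back-solved SD of about 3.5, assumed correlations, equal variances and normal scores.

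Three stronger conclusions do not follow: that the trial is underpowered, that its type I error for alcohol use is inflated, or that the interaction is irrelevant to the hypothesis.

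**What to change.** Before unblinding, name one primary contrast: the between-arm difference in AUDIT at one pre-stated follow-up, adjusted for baseline AUDIT and reported with a 95% CI. Estimate it by ANCOVA at that visit or from a mixed model of the 3- and 12-month scores. State which, because the two need not agree exactly when follow-up is incomplete and 20% loss is expected.

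Twelve months is one possible choice, but nothing in the protocol ranks it above 3 months; the sponsor must decide. Make the other visit secondary and the interaction descriptive. Say what the *t* tests are for. In the sample size section, give the SD and the time point to which the 80% refers. Adjustment for clinic and sex is optional.

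The change needs no new data, since AUDIT is collected at baseline and at each follow-up. The downside is that one visit must be declared decisive, so an effect confined to the other visit would count only as secondary evidence.
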